#### Sample size calculation

Duration of sickness absence until full RTW was chosen as the primary outcome measure and used for sample size calculation. Based on data from a Danish sickness absence study [36], we assumed that 70% would return to work within 6 months (“fail probability” of 0.70). We expected a 40% higher rate of RTW in the intervention group than in the control group, corresponding to a hazard ratio of 1.4. Sample size calculation, using a two-sided significance level of 5% and a power of 80%, indicated a minimum of 397 participants divided equally into the two groups. We decided to include an additional 10% to compensate for drop outs.

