### Participants

The target population were individuals on sick leave from part-time or full-time work or unemployment.

Participants were eligible for the study if they were between 18 and 64 years old and had a SCL-8 AD score ≥5.

Participants were ineligible when they met one or more of the following exclusion criteria: 1) did not communicate in Danish; 2) had been on sick leave due to mental health problems for more than 3 consecutive months during the preceding year; 3) were pregnant; 4) had a supported job/were in job training/in rehabilitation/had retired.

A total of 4,541 individuals were on sick leave and referred to the job centres in the study period. Of the 1,129 eligible individuals, 430 accepted to participate (Figure 1). After randomisation, 30 participants withdrew from the study. RTW data were registered for all participants.

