**Flowchart of the study.**

### Randomisation

The participants were equally randomised (1:1) to one of two parallel groups; the intervention group or the control group. The study was designed as a superiority trial. A computerised random number generator with a block size 4 was used to allocate participants. The programme was prepared by a data manager with no further involvement in the study. The randomisation was carried out by a research assistant who also informed the participants by mail of their allocation.

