### Statistical analysis

It will be studied whether the participants differ from the eligible individuals who declined participation, and if the participants at follow-ups are different from the baseline population in relation to socio demographic and health characteristics. Adherence to the intervention will be described.

The rates of sustainable RTW will be compared between the intervention group and the control group during the first 3 and 6 months after randomisation by means of the pseudo value method [49, 50]. Any effects on psychological symptoms, mental health-related quality of life, and locus of control will be measured in secondary analyses. In those analyses symptoms of depression and anxiety will be the main outcome.

The analyses will be performed using STATA 11 IC (Stata Corp, College Station, TX).

All analyses will primarily be performed on an intention-to-treat basis; however, per-protocol analyses will also be performed [51].

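### The 397 participants and 80% power come from a hazard-ratio calculation, but the planned pseudo-value comparisons have slightly less power at 6 months and clearly less at 3 months

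*Protocol article*

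**What the plan says.** The protocol's Sample size calculation section bases the size on time to full RTW. For the event probability it says "we assumed that 70% would return to work within 6 months", and it expects a 40% higher RTW rate with psychoeducation, "corresponding to a hazard ratio of 1.4". The calculation was done "using a two-sided significance level of 5% and a power of 80" per cent and "indicated a minimum of 397 participants divided equally into the two groups". A margin follows: "We decided to include an additional 10% to compensate for drop outs".

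The Statistical analysis section gives the primary analysis in one sentence: "The rates of sustainable RTW will be compared between the intervention group and the control group" over 3 months and over 6 months from randomisation, by the pseudo-value method. It mentions no Cox model, log-rank test or hazard ratio, and does not say which horizon carries the primary test.

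Two further statements matter. The Randomisation section says "The participants were equally randomised (1:1) to one of two parallel groups". The Participants section reports 430 acceptances and says "RTW data were registered for all participants". The primary outcome itself is defined as a time in days from randomisation to full RTW.

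**The concern.** The calculation and the analysis rest on different tests. A hazard-ratio test uses when each person returned. A pseudo-value comparison at a single horizon, with little or no censoring, uses only whether each person had returned by then, because the pseudo-value reduces to a 0/1 indicator. For the same underlying effect it has less power, and the earlier the horizon, the fewer people have returned and the larger the loss.

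The only power figure in the protocol is 80%. With two comparisons planned and neither named as primary, a reader will attach 80% to both. The risk is mainly at 3 months, where a null result could be taken as evidence of no early effect from a well-powered comparison. The Discussion says the results should help decide whether job centres adopt the programme, so this matters.

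**Working it through.** **Inputs from the protocol.** Two-sided 5%, 80% power, hazard ratio 1.4, 70% RTW by 6 months, 1:1 allocation, minimum N = 397, 430 entered.

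**Inputs assumed.**
- The comparison at each horizon is of cumulative RTW.
- Censoring is negligible.
- The hazard ratio is constant at 1.4, so intervention RTW = 1 − (1 − control RTW)^1.4.
- For 3 months, where no rate is given, the hazard is constant. A range is shown as well.

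**Step 1: reproduce 397.** Events = 4(1.960 + 0.842)² / (ln 1.4)² = 277.3. Dividing by 0.70 gives 396.2, rounded up to 397. The match needs 70% to be the overall event proportion. If 70% were the control arm alone, the intervention arm would reach 81.5% and the average would be 75.7%. The rounded-up 278 events would then need 278 / 0.757 ≈ 367 participants. The text does not say which is meant, so both readings are carried forward.

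**Step 2: RTW proportions implied by a hazard ratio of 1.4.**
- 70% in controls: at 6 months 70.0% vs 1 − 0.30^1.4 = 81.5%. At 3 months control non-return is √0.30 = 0.548, giving 45.2% vs 56.9%.
- 70% overall: at 6 months 64.0% vs 76.0% (average 70%). At 3 months 40.0% vs 51.1%.

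**Step 3: power for the difference in proportions**, with n = N/2 per arm: power = Φ(d/SE − 1.960), SE = √[(p₁(1 − p₁) + p₂(1 − p₂))/n].

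Example, 6 months, 70% in controls, N = 397: d = 0.1147, SE = 0.0426, d/SE = 2.69, power 76.7%. Using the pooled variance under the null gives 76.1%. The table shows pooled to unpooled.

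| Comparison | N = 397 | N = 430 |
|---|---|---|
| 6 months, 70% in controls | 76.1-76.7% | 79.4-79.9% |
| 6 months, 70% overall | 74.9-75.5% | 78.2-78.7% |
| 3 months, constant hazard, 70% in controls | 64.8-65.3% | 68.2-68.7% |
| 3 months, constant hazard, 70% overall | 60.2-60.7% | 63.7-64.1% |

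For comparison, a hazard-ratio test with 70% events has 80.1% power at 397 and 83.1% at 430.

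**Step 4: 3 months without the constant-hazard assumption.** Keep the hazard ratio at 1.4 and let control RTW at 3 months vary.
- 30% vs 39.3%: about 50% power at 397 and 53% at 430.
- 55% vs 67.3%: about 71-72% at 397 and 75% at 430.

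The whole range is below 80%.

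**Step 5: other targets that pseudo-values could have.** Simulated power for a restricted mean over 6 months was 75-79% at 397. A joint complementary log-log model over both horizons, which estimates a hazard ratio, gave 77-82% at 397 in a grouped-data simulation.

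**The case against.** The strongest reply has four parts.

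- **The arithmetic is right.** This stands. A reader might infer that 397 is miscalculated; it follows exactly from the stated inputs.
- **The analysis is not said to compare proportions.** Also true. The section speaks of rates, gives no link function or estimand, and may leave these to an analysis plan that is not shown. Pseudo-values can also target a restricted mean or, modelled jointly over several times, a hazard ratio. Near-complete follow-up is likewise inferred from the statement on registered RTW data. It is therefore too strong to say that the 80% belongs to a test that is definitely not planned: a joint model would roughly recover it. But cumulative RTW at each horizon is the natural reading of two separately named periods, and the restricted mean does not reach 80% at 397.
- **The trial has more than 397 people.** With the planned 10% (397 × 1.1 ≈ 437) the 6-month power is about 79-81%, and with 430 about 78-80%. A reader might infer that the trial is materially underpowered at 6 months; the figures do not support that. The margin was, however, justified by drop-outs and not by a less efficient test.
- **No power is claimed at 3 months.** Correct: the calculation refers to return within 6 months, and any 3-month figure rests on an assumed rate. What remains is that both horizons are planned on equal terms, with one power figure and nothing to separate them.

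**Conclusion.** The point holds as a mismatch between the basis of the sample size and the planned analysis, not as an error in the number 397. Read as cumulative RTW at each horizon with little censoring, 6-month power is about 75-77% at 397 and 78-80% at 430, at most about 2 points below the stated 80% for the participants actually entered. At 3 months the shortfall is material: about 60-65% at 397 and 64-69% at 430 under constant hazard, or about 50-72% and 53-75% if control RTW at 3 months is 30-55%. The size of the 3-month loss depends on that assumed rate; its direction does not within the range shown.

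A reader might also conclude that the comparison cannot address shorter absence, or that the primary test must become a Cox or log-rank test. Neither follows. A higher chance of having returned by 3 and 6 months is evidence of shorter absence within that window. The pseudo-value method is defensible, and a single hazard ratio would bring in a proportional-hazards assumption that it need not make.

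**What to change.** Keep the pseudo-value method. In the Statistical analysis section, name the 6-month comparison as primary and the 3-month comparison as supportive. Beside the sample size calculation, state that 397 was derived for a hazard ratio of 1.4 with 70% events, and give the power of the planned comparison: about 75-77% at 397 and about 78-80% at 430 for 6 months, with the 3-month figures labelled as resting on an assumed RTW rate and shown as a range. A time-to-event analysis, or a joint hazard-ratio model over both horizons, can be added as a sensitivity analysis that matches the sample size basis. It should not replace the primary method, because recruitment has ended and that would change the pre-stated analysis.

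The cost is a few sentences and a slightly less favourable stated power. No further participants or data are needed.

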### Statistical analysis

It will be studied whether the participants differ from the eligible individuals who declined participation, and if the participants at follow-ups are different from the baseline population in relation to socio demographic and health characteristics. Adherence to the intervention will be described.

The rates of sustainable RTW will be compared between the intervention group and the control group during the first 3 and 6 months after randomisation by means of the pseudo value method [49, 50]. Any effects on psychological symptoms, mental health-related quality of life, and locus of control will be measured in secondary analyses. In those analyses symptoms of depression and anxiety will be the main outcome.

The analyses will be performed using STATA 11 IC (Stata Corp, College Station, TX).

All analyses will primarily be performed on an intention-to-treat basis; however, per-protocol analyses will also be performed [51].

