### Primary outcome

#### Sickness absence duration

Time to full RTW was the primary outcome of the study and was measured by register data from the job centres. It was defined as the period (in days) between randomisation and to *full-time* RTW for at least 4 weeks without (partial or full sickness absence) recurrence. Full return to work was operationalised as not receiving sickness benefits.

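### The primary outcome is compared at 3 and at 6 months without saying which comparison decides the trial, although the sample size rests on one two-sided 5% test at 6 months

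*Protocol article*

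**What the plan says.** The section on the primary outcome names one endpoint: "Time to full RTW was the primary outcome of the study and was measured by register data from the job centres". It counts days from randomisation to full RTW sustained for at least 4 weeks and gives no analysis horizon.

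The Statistical analysis section gives the only described comparison of this endpoint. Rates of sustainable RTW are compared between the groups "during the first 3 and 6 months after randomisation by means of the pseudo value method". Neither horizon is called primary, and no testing order or division of the significance level is given. The same paragraph does rank the secondary measures, making depression and anxiety symptoms the main ones.

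The only significance level appears under Sample size calculation, "using a two-sided significance level of 5% and a power of 80"%. That calculation has one horizon, "we assumed that 70% would return to work within 6 months", and one effect, "corresponding to a hazard ratio of 1.4". It "indicated a minimum of 397 participants divided equally into the two groups".

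**The concern.** One endpoint with two unranked comparisons leaves the trial without a stated decision rule. A 6-week course could plausibly produce a difference at 3 months that has faded by 6, or one that appears only later. Under the article's wording, either result could be presented as showing faster RTW, and conflicting results have no agreed reading.

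If both comparisons are tested at the level used for the sample size, the primary conclusion no longer carries a 5% error rate. The Strengths and limitations section expects the result to inform decisions on implementation in the job centres, so the rule for calling the trial positive matters.

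**Working it through.** **1. The plan's own figure.** Inputs from Sample size calculation and Randomisation: hazard ratio 1.4, two-sided 5%, power 80%, event probability 0.70, allocation 1:1.

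- Events (Schoenfeld) = 4 × (1.960 + 0.842)² / (ln 1.4)² = 277.3, rounded up to 278.
- Participants = 278 / 0.70 = 397.1.

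This matches the stated 397. The sample size therefore corresponds to one 5% test at the 6-month horizon.

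**2. Upper bound for two tests at 5%.** If they were independent: 1 − 0.95² = 9.75%.

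**3. Allowing for correlation.** Let F3 and F6 be the proportions back at work by 3 and 6 months. Without censoring, the correlation of the two between-group contrasts under no effect is

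ρ = √[ F3(1 − F6) / (F6(1 − F3)) ].

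F6 = 0.70 comes from the article. F3 is not given. Assuming a constant hazard, F3 = 1 − 0.30^(1/2) = 0.452, so

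ρ = √[ 0.452 × 0.30 / (0.70 × 0.548) ] = 0.595.

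The familywise error is the bivariate normal probability that |Z3| or |Z6| exceeds 1.96. The chance of a false claim of benefit is the probability that Z3 or Z6 exceeds +1.96, with positive values favouring psychoeducation.

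| Reading | F3 (assumed) | ρ | Any false difference | False benefit |
|---|---|---|---|---|
| Cumulative RTW | 0.20 | 0.327 | 9.5% | 4.7% |
| Cumulative RTW | 0.30 | 0.429 | 9.3% | 4.6% |
| Cumulative RTW, constant hazard | 0.452 | 0.595 | 8.8% | 4.4% |
| Cumulative RTW | 0.55 | 0.724 | 8.2% | 4.1% |
| Cumulative RTW | 0.60 | 0.802 | 7.8% | 3.9% |
| Log-rank type contrast cut at each horizon, ρ = √(F3/F6) | 0.452 | 0.804 | 7.8% | 3.9% |
| Restricted mean time to RTW, constant hazard | 0.452 | 0.890 | 7.1% | 3.6% |

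A simulation of 200,000 null trials with 215 per arm, at F3 = 0.452 and F6 = 0.70, gave 8.9% for any false difference.

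**4. The alternatives.** One named horizon restores 5% and leaves 397 as it stands. Keeping both horizons as equal claims at 2.5% each holds the familywise error at about 4.5% (ρ = 0.595), but the 278 planned events then give about 71% power for a hazard ratio of 1.4. Restoring 80% would take 336 events, or 336 / 0.70 = 480 participants before the dropout allowance.

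**The case against.** Five points can be made against this.

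- **Separate tests are not stated.** Pseudo-value regression can put both time points in one model with a common group effect, which is a single test. The article describes neither version, and the 5% per comparison is carried over from the sample size section. This stands, and it is why the error figures are conditional.
- **The article leans towards 6 months.** The sample size uses that horizon, and the baseline question on recovery expectations uses it too. The 3-month result may be meant only as an earlier look at the same curve. That reading is reasonable, but a power assumption does not name the deciding test.
- **The order may be settled elsewhere.** Testing order is commonly left to a fuller plan, which is not shown. This lowers confidence. It does not remove the point, because the article itself fixes two comparisons and ranks neither.
- **A flat 9% would overstate precision.** A reader might take 9% as the chance of a false claim that psychoeducation works. The documents do not support that. The two-sided figure also counts results favouring usual care, whereas the hypothesis is shorter absence. The matching figure is about 4% to 5% against 2.5%, and the two-sided figure falls to about 7% if the target is a restricted mean.
- **Nothing shows an intention to choose.** A reader might infer that the time point will be picked once the data are seen. The text leaves room for that but does not provide for it, and both horizons are stated in advance.

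**Conclusion.** The point holds in a limited form. The article compares its single primary outcome at two horizons and does not say which one decides, while its sample size supports one two-sided 5% test at 6 months. If the horizons are tested separately at 5%, the two-sided familywise error is about 7% to 9.5%, with 8.8% as the central value for cumulative RTW under a constant hazard. A false claim of benefit then occurs about 4% to 5% of the time (3.6% to 4.7% over the cases calculated) against a nominal 2.5%.

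These sizes rest on three assumptions: separate tests at 5% each, the unstated 3-month proportion (0.20 to 0.60 examined), and the quantity the pseudo-values target. On every separate-test reading examined the error exceeds 5%; under a single joint test it would not. The sample size itself is not in question. This should be fixed, but it does not invalidate the design, and confidence is moderate.

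**What to change.** State that the between-group comparison of sustained full RTW at 6 months is the single primary test, at two-sided 5%. Make the 3-month comparison secondary: either test it at 5% only if the 6-month test is significant, which keeps the familywise error at 5%, or report it as an estimate with a confidence interval and no claim attached. Say in the same sentence which quantity the pseudo-values estimate. If a fuller plan already does this, refer to it. Otherwise date the statement before outcomes are compared by group.

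The cost is one sentence. The sample size of 397 plus the dropout allowance, the power, the data collection and the conduct of the trial are unchanged. The small downside is that a difference present only at 3 months cannot carry the primary claim.

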### Ethical considerations

All participants were offered treatment as usual according to their individual needs, i.e. RTW activities offered by the job centres and treatment from health professionals. Participation was voluntary, and project information was given both verbally and in writing. The participants were informed about their rights to decline participation and to withdraw with no consequences in terms of their sickness absence benefits.

Previous research has not indicated that PE induces risk to the participants. However, it has been discussed whether information about possible mental symptoms can implant expectations of pathology and dysfunction [10]. Compared to traditional PE, the intervention in this study focused on diagnosis to a less extent. Therefore, we expect negative expectations of pathology and dysfunction to be rare.

During the sessions, the psychiatric nurses were aware of the participants’ reactions, and, if needed, they talked to them. If the psychiatric nurses observed a need for additional treatment, they could encourage the participants to see their general practitioner or refer them to a psychiatrist ([name]).

All participants were assigned an identification number and were treated anonymously in all analyses. Papers and electronic documentation with names and personal identification numbers were stored securely in locked cabinets or on a password-protected computer.

The study has been notified to and approved by the Danish Data Protection Agency (http://www.datatilsynet.dk). According to the Danish National Committee on Biomedical Research Ethics (written communication), the intervention did not need ethic approval as it did not include biomedical research. The study is registered at Clinical Trials.gov (NCT01637363).

## Discussion

This trial will evaluate the effect of PE on RTW among individuals on sick leave and at risk of having a mental disorder. We will assess the impact of the intervention on sickness absence duration, psychological symptoms, mental health-related quality of life and locus of control.

The study will assess the effectiveness rather than the efficacy of the RTW intervention. Thus, it will evaluate what is possible in practice. As a consequence, participants were included based on a simple screening instrument which is easily applicable for the social workers. Not all the participants may have a mental disorder, meaning that the included individuals can be very different with some suffering from a major depression and some having distress. On the other hand, if individuals on sick leave with a specific diagnosis had been included, then the participants had to be screened by their general practitioner, which deviates from usual practice in the job centres.

Individuals who had been on sick leave due to mental health problems for more than three consecutive months during the preceding year and those without a paid job were excluded. This was done based on the assumption that the intervention would probably not fully accommodate the needs of these individuals. Furthermore, a previous Danish study conducting a psychiatric examination found that the feedback and information based on the examination was most effective for individuals on sick leave from full-time work and without a psychiatric sick leave diagnosis [52].

### Psychoeducation

The topics in the PE course should be versatile to address all the different needs of this heterogeneous group. Consequently, different health professionals were used to provide the individuals with broad information. PE has been documented to be meaningful in settings where a multidisciplinary team effort is available [12]. The psychiatric nurses were highly experienced in PE while the social worker, the psychologist and the physiotherapist had experience in working with individuals on sick-leave. PE can be administered by therapists from various disciplines without extensive training [12]. The use of different health professionals may also be important to avoid that the effect may be ascribed to the influence of a personality of a single professional, which cannot be replicated in other settings.

We decided to provide the courses as a slow-open group and not as a closed group. To our knowledge, PE has not previously been carried out in this way. We chose this setting to be able to offer the intervention as fast as possible since it has been documented to be important [9]. If closed groups had been used, participants could have waited up to 6 weeks to start the intervention. It is plausible that the waiting time could worsen their symptoms. To compensate for the weekly inclusion of new participants, the same psychiatric nurse was present for six successive sessions. She welcomed new participants and was familiar with the group.

